### Statistical analysis

Statistical analysis of the RMTs and MEPs will be performed with Statistical Package for Social Science (SPSS) software for Windows, version 17.0 (SPSS Inc., Chicago, IL, USA). D’Agostino’s test for normally distributed variables and Levene’s test for homogeneity of variance will be applied. For healthy participants, if measurement data are normally distributed, then Bonferroni’s test will be used to analyse between-group differences for each participant pre- and post-electroacupuncture or sham electroacupuncture. Otherwise, Kruskal-Wallis’ H test for a nonparametric distribution will be used. The level of significance is set at 5% for all comparisons. For patients with post-stroke hemiplegia, if the measurement data are normally distributed, then an independent *t* test will be used to analyse between-group differences for each participant pre- and post-electroacupuncture or sham electroacupuncture. Otherwise, the Wilcoxon rank-sum test for a nonparametric distribution will be used. The level of significance will be set at 5% for all comparisons.

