### Study procedure

The healthy volunteers who consent to participate in the study will complete magnetic resonance imaging (MRI) in Guangdong 999 Brain Hospital, and finish the MMSE, physical examination, and BMI evaluation in an examination room at South China Research Center for Acupuncture and Moxibustion, Medical College of Acu-Moxi and Rehabilitation, Guangzhou University of Chinese Medicine. The patients with post-stroke hemiplegia who consent to participate in the study will undergo MRI, National Institutes of Health Stroke Scale (NIHSS), FMA, Barthel index, and physical examination at a rehabilitation room in Guangdong 999 Brain Hospital. All participants will sit on a treatment chair facing the neuroimaging navigation and TMS machine to enable the location of the correct brain regions.

This study will be divided into the following parts:

Part 1: Effect of different frequencies of electroacupuncture on the excitability of M1 in healthy participants. Firstly, the cortical stimulation will be performed on the left and right M1 of all healthy participants while recording the RMTs and MEPs of bilateral thenar muscles. And then, they will receive 2-Hz, 50-Hz, 100-Hz, or sham electroacupuncture intervention on their left limbs for 20 minutes to explore the optimal frequency. Finally, the RMTs and MEPs both will be tested immediately after intervention within 5 minutes again.

Part 2: Effect of opposing needling on the excitability of M1 in patients with post-stroke hemiplegia. Firstly, the cortical stimulation will be performed on the left and right M1 of patients with post-stroke hemiplegia before the treatments while recording the RMTs and MEPs of bilateral thenar muscles. And then, on the premise of the same conventional treatments and rehabilitation trainings, all the patients will opposing needling as the optimal frequency of electroacupuncture acquired from Part 1 or sham electroacupuncture. After ten opposing needling treatments or ten sham electroacupuncture interventions, the RMTs and MEPs both will be detected again.

Part 3: The physiological and pathological data will be combined to determine the relationship between M1 excitability and stroke rehabilitation, explore the effect of opposing needling on M1 excitability, propose a possible hypothesis for the treatment of post-stroke hemiplegia by opposing needling, and explore the possibility of using M1 excitability to predict stroke recovery.

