### Outcome measures

#### Primary outcome measure

The primary outcome measure will be the per cent change in the RMTs of the thenar muscles at baseline and after the intervention. The RMTs of the thenar muscles will be delivered by a TMS pulse every 30 s bilaterally to the left or right M1, respectively, for 10 pulses in the fully relaxed state. The MEP of the thenar muscles should be greater than or equal to 50 μV for at least half (5/10) of the TMS pulses. The RMT is defined as the minimum intensity that is needed to elicit the MEP ≥ 50 μV in at least 50% of the pulses.

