### Sample size calculation

The sample size for the 2-Hz, 50-Hz, 100-Hz, and sham electroacupuncture groups was 20, which was calculated according to the following statistical formula: n = $$ {\upvarphi}^2\Big(\sum {\mathrm{S}}_{\mathrm{i}}^2/ $$g)/[$$ \sum {\left({\overline{\mathrm{X}}}_{\mathrm{i}}-\overline{\mathrm{X}}\right)}^2/\left(\mathrm{g}-1\right)\Big] $$, where g represents the number of groups and group allocation ratios are equal. Based on the preliminary experiment, the average RMT reductions in each group were expected to be − 4.44, − 3.33, − 1.75, and − 0.91, with standard deviations of 3.69, 2.89, 3.40, and 1.92, respectively. The *P*-value for the two-sided test was 0.05, and the test power was 80%. Thus, using PASS 15 software, the optimal sample size was 72. Considering a 10% dropout rate, a total of at least 80 participants would have to be included, with 20 participants included in each group.

For patients with post-stroke hemiplegia in the opposing needling or conventional treatment groups, the sample size was 20 based on the statistical formula *n* = $$ {\left[\frac{\left({Z}_{\propto }+{Z}_{\beta}\right)\upsigma}{\updelta}\right]}^2 $$. The main primary outcome measure is RMT. *δ* is the RMT of the thenar muscles, and according to our previous trials, the minimum clinically significant RMT value was estimated to be 3.57 [24]. Thus, *δ* was estimated to be 3.57. ∝is the significance level; *β* is the power of the test. In this study, ∝= 0.05, *Z*_∝_= 1.96, *β* = 0.80 (80%), and *Z*_*β*_ = 0.84, while σ was estimated at 3.67. With the PASS 15 software, the optimal sample size of the opposing needling and conventional treatment groups was calculated as 18 cases. Considering an overall dropout rate of 10%, including cases lost to follow-up and patients refusing to follow-up, at least 20 participants would be required in the treatment and control groups. Thus, at least 40 patients with post-stroke hemiplegia would have to be recruited for the study.

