### Effect of different frequencies of electroacupuncture on regulation of stroke

Compared to traditional acupuncture, electroacupuncture has the advantage of high reproducibility of the therapeutic effects, the precision of stimulation parameters and a significant reduction in labour. This new acupuncture therapy is becoming more and more popular. Different frequencies of electroacupuncture could produce different effects. For neurological reconstruction, electroacupuncture could promote the expression of NGF and BDNF in the hippocampal CA3 region of cerebral ischemic rats, and the 50-Hz electroacupuncture effect was more obvious [32]. For cerebral blood flow, the electroacupuncture in both 2 and 15 Hz groups induced the increase of cerebral blood flow in rats [33]. Besides, electroacupuncture could improve local cerebral blood perfusion and brain cell functions, and the effect of 2/15 Hz and 100 Hz were better [34]. For motor functional recovery, low-frequency electroacupuncture could promote recovery of motor function after focal cerebral ischemic injury in rats [35]. Electroacupuncture in the 2-Hz group had an obvious effect on dysphagia after stroke in mice [36]. However, there are few researches on the effect of different frequencies of electroacupuncture or opposing needling on motor cortex excitability in healthy participants or in patients with post-stroke hemiplegia. The effect of different frequencies of electroacupuncture on bilateral motor cortex excitability should be studied further. Due to even at the maximum stimulation in TMS, the affected hemispheres of some patients with post-stroke hemiplegia often fail to induce MEPs. Thus, we design this study to explore the effect of different frequencies of electroacupuncture on bilateral motor cortex excitability in healthy participants and then acquire the optimal frequency of electroacupuncture for motor cortex excitability. Lastly, we will apply this frequency of electroacupuncture to patients with ischemic stroke to explore its effect on motor cortex excitability.

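### The planned RMT comparison leaves out baseline RMT; adjusting for it would usually gain some precision at small cost

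*Protocol article*

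**What the plan says.** The outcome section of the protocol article fixes the scale: "The primary outcome measure will be the per cent change in the RMTs of the thenar muscles at baseline and after the intervention".

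The Statistical analysis section fixes the tests. For patients, an independent t "test will be used to analyse between-group differences for each participant pre- and post-electroacupuncture or sham electroacupuncture", with the Wilcoxon rank-sum test if the data are not normal. For healthy participants the same sentence is used with Bonferroni's test, and then: "Otherwise, Kruskal-Wallis’ H test for a nonparametric distribution will be used". No covariate is named in either part, and the section does not itself say on which scale RMT is tested.

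Baseline RMT is planned for both populations under Study procedure. In Part 1, "the cortical stimulation will be performed on the left and right M1 of all healthy participants while recording the RMTs and MEPs"; in Part 2, stimulation is "performed on the left and right M1 of patients with post-stroke hemiplegia before the treatments while recording the RMTs and MEPs". The Discussion adds a limit: "the affected hemispheres of some patients with post-stroke hemiplegia often fail to induce MEPs".

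The Sample size calculation for patients states that "the minimum clinically significant RMT value was estimated to be 3.57", takes a standard deviation of 3.67, and arrives at 18 per group, or 20 after 10% dropout. Neither value is given a unit or said to be per cent or absolute.

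**The concern.** When the same quantity is measured before and after treatment, a simple comparison of changes fixes the weight given to baseline in advance. A model that estimates that weight (ANCOVA) usually has smaller residual variance and takes out chance differences in baseline between arms. The arms here are small (20 each), and the article describes no stratification of the randomisation. The baseline is being collected anyway, but the named tests use it only to form the change.

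Precision matters in both parts. Part 1 chooses the electroacupuncture frequency used in Part 2. In Part 2, patients enter up to 6 months after stroke, and the Discussion reports that thresholds on the affected side tend to fall over the first months. Baseline RMT and time since stroke may therefore carry variation that an unadjusted test leaves in the error term.

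The unstated scale adds a difficulty. If 3.57 is in RMT points, it is 3.57/45 = 7.9% at a mean baseline of 45 and 3.57/60 = 6.0% at 60 (both baselines assumed). The effect the trial is sized for cannot be mapped to the primary outcome from the article alone.

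**Working it through.** **1. The plan's own figure (patients).** Inputs from the Sample size calculation: difference 3.57, SD 3.67, two-sided 5% (Z = 1.96), 80% power (Z = 0.84).

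- Normal approximation for two groups: n = 2 × [(1.96 + 0.84) × 3.67 / 3.57]² = 2 × 8.285 = 16.6, so 17 per arm.
- Two-sample t test (noncentral t): power 0.785 at 17 per arm and 0.809 at 18.
- Dropout: 18 / 0.90 = 20.

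The stated 18 and 20 are reproduced, and the unadjusted test reaches its target.

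**2. Adjusting for baseline (patients, 18 per arm).** Assumptions, not in the article: 3.67 is the SD of the change in RMT points, variances before and after are equal, and the pre-post correlation is rho. The change has variance 2σ²(1 − rho); the residual after adjustment has variance σ²(1 − rho²). Their ratio is (1 + rho)/2, so the residual SD is 3.67 × √[(1 + rho)/2]. Power uses the noncentral t with 2n − 3 = 33 degrees of freedom. The baseline SD implied by each rho is 3.67 / √[2(1 − rho)].

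| rho (assumed) | implied baseline SD | residual SD | power, adjusted | n per arm for 80% |
|---|---|---|---|---|
| 0.5 | 3.67 | 3.178 | 0.905 | 14 |
| 0.7 | 4.74 | 3.384 | 0.867 | 16 |
| 0.8 | 5.80 | 3.482 | 0.847 | 16 |
| 0.9 | 8.21 | 3.577 | 0.828 | 17 |
| 0.95 | 11.61 | 3.624 | 0.818 | 18 |

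Against 0.809 the gain is about 10, 6, 4, 2 and 1 points. At rho = 1 the power is 0.8085, a loss of 0.1 point from the extra degree of freedom.

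**3. Simulation against per cent change itself.** 20,000 trials per setting, 18 per arm, assumed mean baseline 45 or 60, SD of change before any treatment effect 3.67. Entries are power for per cent change / adjusted model.

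| rho | additive, 45 | additive, 60 | proportional, 45 | proportional, 60 |
|---|---|---|---|---|
| 0.5 | 0.822 / 0.896 | 0.817 / 0.896 | 0.797 / 0.895 | 0.799 / 0.892 |
| 0.7 | 0.815 / 0.856 | 0.811 / 0.852 | 0.795 / 0.857 | 0.802 / 0.856 |
| 0.8 | 0.814 / 0.834 | 0.815 / 0.837 | 0.779 / 0.831 | 0.793 / 0.834 |
| 0.9 | 0.810 / 0.823 | 0.811 / 0.815 | 0.761 / 0.813 | 0.784 / 0.816 |
| 0.95 | 0.779 / 0.810 | 0.798 / 0.802 | 0.700 / 0.803 | 0.756 / 0.806 |

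The adjusted model is ahead of per cent change in every setting: by 0.4 to 8 points for an additive effect and 3 to 10 for a proportional one. Its simulated power lies 0.5 to 1.7 points below the formula in step 2, which leaves out the small loss caused by chance baseline imbalance. Against raw change with an additive effect, the simulated gain is 8.5 to 8.7 points at rho 0.5. At rho 0.95 it turns into a loss of 0.4 to 0.5 point (0.813 against 0.810; 0.806 against 0.802).

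**4. Healthy participants, 18 per group.** Pooled SD = √[(3.69² + 2.89² + 3.40² + 1.92²)/4] = 3.05. One-way ANOVA on the stated means has power 0.889. With adjustment it is 0.961, 0.921 and 0.905 at rho 0.5, 0.8 and 0.9.

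**The case against.** The strongest reply is that nothing is broken. Under 1:1 randomisation a comparison of changes is valid, chance imbalance adds noise rather than bias, and the planned size delivers its power. That stands in full.

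The gain also depends on a correlation the article does not give. With the SD of change held at 3.67, a low rho implies a narrow spread of baseline values (3.67 points at rho 0.5, 8.21 at 0.9). The Discussion describes generally raised thresholds and non-responding hemispheres on the affected side, and nothing in the article supports the low-rho end in particular. The power figures further assume that 3.57 and 3.67 are RMT points; if they are percentages, the figures do not carry over as they stand.

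Three stronger readings are tempting and are not supported:

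- That adjustment is free. It uses a degree of freedom, needs a linear model, has no direct counterpart in the rank-test fallback, and changes the stated primary quantity after recruitment began on 1 January 2020.
- That baseline RMT will be available in everyone. The Discussion says some affected hemispheres yield no response. Per cent change is equally undefined there, so this does not favour either analysis, and adjustment does not cure it.
- That per cent change is harmful in itself because it over-corrects or skews at low baselines. The article gives no baseline values, and with an additive effect the simulated cost of the per cent scale against raw change is nil or slight except at rho 0.95.

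It may also be said that covariates belong in a statistical analysis plan that is not shown. But the article names the tests, so a plan using a baseline-adjusted model would depart from it.

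**Conclusion.** The point holds as an efficiency improvement, not as an error. The article names unadjusted tests of a per cent change outcome while planning to collect the baseline value that would sharpen the comparison. In the patient part the gain in power by formula runs from about 10 points at rho 0.5 to about 1 at rho 0.95, and simulation puts it somewhat lower. The adjusted model was not below per cent change in any setting examined, and its losses against raw change were half a point or less. All of this rests on an assumed correlation, assumed mean baselines in the simulation, and the reading of 3.57 and 3.67 as RMT points of change. A reader might infer that the trial is underpowered or its planned comparison biased; the reproduced 18 per arm and the randomised design rule that out.

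**What to change.** For each part and each hemisphere, make the primary analysis a linear model of post-intervention RMT on group and baseline RMT of the same hemisphere. In Part 2, time since stroke may be added as a further covariate. Keep the Bonferroni adjustment for the Part 1 pairwise comparisons. Report per cent change as a descriptive summary. State whether 3.57, 3.67 and the Part 1 means and SDs are RMT points or per cent, and say what becomes of the rank-test fallback, for instance as a sensitivity analysis.

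No new data are needed. The cost is one degree of freedom and a headline result in RMT points instead of per cent. Because that alters the stated primary analysis of a trial already recruiting, it should be documented as a protocol amendment made before unblinding.

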### Patient and public involvement

Patients and the public are not involved in the design or conduct of the study or the outcome measures, and the burden of intervention will not be assessed by the trial participants. Individuals involved in the consultations related to the trial design will not be included as trial participants.

## Discussion

### Acupuncture point selection

Previous studies suggested that the most commonly used meridians in clinical treatment of post-stroke hemiplegia are the large intestine meridian of hand-Yangming (LI), stomach meridian of foot-Yangming (ST), and gallbladder meridian of foot-Shaoyang (GB); the most commonly used acupoints are LI11, ST36, LI4, etc. [31]. According to Traditional Chinese Medicine theory, hemiplegia after stroke belongs to the category of flaccidity syndromes, and *The Huangdi’s Classic of Internal Medicine* noted that treatment for flaccidity is aimed at the Yangming meridian. The Yuan primary point is an acupuncture point that represents this meridian and also one of the most commonly used acupuncture points. Therefore, we will select the two of the most commonly used acupuncture points from LI and ST, LI11 and ST36, and choose the Yuan primary points of LI and ST, LI4 and ST42.

### Effect of different frequencies of electroacupuncture on regulation of stroke

Compared to traditional acupuncture, electroacupuncture has the advantage of high reproducibility of the therapeutic effects, the precision of stimulation parameters and a significant reduction in labour. This new acupuncture therapy is becoming more and more popular. Different frequencies of electroacupuncture could produce different effects. For neurological reconstruction, electroacupuncture could promote the expression of NGF and BDNF in the hippocampal CA3 region of cerebral ischemic rats, and the 50-Hz electroacupuncture effect was more obvious [32]. For cerebral blood flow, the electroacupuncture in both 2 and 15 Hz groups induced the increase of cerebral blood flow in rats [33]. Besides, electroacupuncture could improve local cerebral blood perfusion and brain cell functions, and the effect of 2/15 Hz and 100 Hz were better [34]. For motor functional recovery, low-frequency electroacupuncture could promote recovery of motor function after focal cerebral ischemic injury in rats [35]. Electroacupuncture in the 2-Hz group had an obvious effect on dysphagia after stroke in mice [36]. However, there are few researches on the effect of different frequencies of electroacupuncture or opposing needling on motor cortex excitability in healthy participants or in patients with post-stroke hemiplegia. The effect of different frequencies of electroacupuncture on bilateral motor cortex excitability should be studied further. Due to even at the maximum stimulation in TMS, the affected hemispheres of some patients with post-stroke hemiplegia often fail to induce MEPs. Thus, we design this study to explore the effect of different frequencies of electroacupuncture on bilateral motor cortex excitability in healthy participants and then acquire the optimal frequency of electroacupuncture for motor cortex excitability. Lastly, we will apply this frequency of electroacupuncture to patients with ischemic stroke to explore its effect on motor cortex excitability.

### Influence of the corpus callosum on excitability/inhibition of unaffected and affected hemispheres

The connection between the brain and the limbs is bilateral; 80% of the nerve fibres are crossed, which dominate the movement of the contralateral limb, while a small part is not crossed, which directly descends to form the anterior bundle of the cortical spinal cord and dominates the movement on the same side. The corpus callosum, which connects the two hemispheres of the brain, is the largest white matter body in the mammalian brain and contains more than 200 million myelinated axon fibres [37]. The corpus callosum is responsible for information transmission and functional integration between the two hemispheres [38]. Researchers who supported the corpus callosum excitatory model believed that the corpus callosum transmits excitatory information between the two hemispheres and that it can activate the unstimulated cerebral hemisphere, further promoting an exchange of information between the two hemispheres, and facilitating the integration of the functions of the two hemispheres. For patients after stroke, some TMS studies have suggested that the activity in the residual networks in the unaffected hemisphere may contribute to functional recovery after stroke by substituting for the functions lost by the damaged area. However, the interhemispheric competition model suggested exactly the opposite. This model assumes the presence of a mutual, balanced inhibition between the hemispheres in the healthy brain. Damage to the hemisphere by a stroke disrupts this balance, and inhibition of the unaffected hemisphere by the affected hemisphere is reduced, resulting in increasing inhibition of the affected hemisphere by the unaffected hemisphere [39]. One study suggested that patients exhibit over activity in their unaffected M1 after stroke and show high levels of neural excitability, while the affected M1 exhibits a low excitatory level [40]. Another study showed that skin anaesthesia in the unaffected hands of stroke patients can lead to improved behaviour of the affected hands, which supported the interhemispheric competition model [41]. However, the two opposing theories mentioned above may be oversimplified or even incorrect. To better explain the relationship between the balance and functional recovery of the two hemispheres in pathological conditions, Giovanni Di Pino proposed a bimodal balance–recovery model. This model links interhemispheric balancing and functional recovery to the structural reserve spared by the lesion. The proposed ‘structural reserve’, which was described the remaining functional motor output, determined the amount of recovery limited by interhemispheric competition and contributed to the recovery in an individual patient [39]. The rebalancing of interhemispheric competition may play an important role in the process of motor recovery. Previous studies have extensively studied the effects of the affected cerebral hemisphere to better understand changes in motor network activity after stroke, but few studies have examined the effects of the unaffected brain hemispheres. The motor recovery after ischemic stroke in the primary motor cortex may occur partly through training-enhanced reorganisation in undamaged premotor areas, enabled by reductions in cortical inhibition [42]. One study suggested that the restoration of function after stroke is associated with biphasic recruitment of peri- and contralesional functional fields in the brain [43], that the connectivity patterns in the unaffected hemisphere more accurately reflect the behavioural conditions than those in the affected hemisphere [44], and that in comparison with the unaffected hemisphere, the affected hemisphere shows reduced connections from the superior parietal cortex to M1 and supplementary motor cortex [45]. An acupuncture study showed that acupuncture at Yanglingquan (GB34) on the affected limb can reduce compensatory activity in the healthy side of the brain. These studies have shown that the unaffected hemisphere plays an important role in stroke recovery.
